**Methods:**

Sixty amateur runners will be randomly allocated to one of two groups: high-load exercise group (HLG) and moderate-load exercise group (MLG). The HLG will start the treatment with calf exercises with 55% of 1 repetition maximum (1RM) and progressively increase the exercise load in 12 weeks to 90% 1RM. The MLG will perform exercises with 55% 1RM during the 12 weeks of intervention. The RM load will be reassessed every 2 weeks, and the total training volume (total repetitions and tendon time under tension per week) will be the same in both groups. Both groups will also perform strengthening exercises for the quadriceps and gluteal muscles. The primary outcome will be symptom severity (Victorian Institute of Sport Assessment−Achilles), which will be evaluated at baseline, at week 6, at week 12 (end of intervention), and 6 months after the intervention. Pain will be evaluated using the visual analogue scale during the same time points. Secondary outcomes will include peak isometric strength of ankle, knee, and hip muscles, function of plantar flexor muscles, quality of life, and perception of improvement. Results will be analyzed under the intention-to-treat principle using generalized estimating equations (GEE) and Bonferroni-adjusted post hoc tests.

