### Sample size calculation

To determine the study sample size, a calculation was made considering a confidence level (α) of 95%, a power (β) of 80%, and a difference between groups in the Victorian Institute of Sport Assessment-Achilles (VISA-A) at 12 weeks of 14 points [24]. The standard deviation used in the calculations was obtained from a similar clinical trial that used this same variable as the primary outcome [23]. Using this information, calculations for linear mixed models indicated a sample size of 54 individuals (27 per group). Considering a loss of 10%, we reached a total number of 60 individuals, with 30 in each group.

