### Statistical analysis

The data will be analyzed by a researcher who will remain blind to group allocation. The Statistical Package for the Social Science software (version 17.0; SPSS Inc, Chicago, IL) will be used to analyze the results. To assess the normality of data, the Shapiro-Wilk test will be used. Outcome measures will be analyzed using generalized estimating equations (GEE) to identify main effects of group and time, and group-by-time interactions. Bonferroni-adjusted post hoc tests will be used when appropriate. The results will be presented as mean differences and 95% confidence intervals (CI). All data will be analyzed using the intention-to-treat principle, and in the event of missing data, a regression-based imputation technique will be used [55].

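### Bonferroni for the post hoc tests is valid, but Holm's step-down version gives the same error control, is never less powerful, and is a cheap improvement when several visits differ

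*Protocol article*

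**What the plan says.** The last paragraph of the Introduction makes between-group effects at 6 weeks, 12 weeks and 6 months primary objectives, for pain and symptom severity. The Outcomes section schedules VISA-A and pain at each of those visits as well as at baseline.

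The Statistical analysis section plans "generalized estimating equations (GEE) to identify main effects of group and time, and group-by-time interactions", then adds "Bonferroni-adjusted post hoc tests will be used when appropriate". The Abstract (Methods) repeats the choice: "using generalized estimating equations (GEE) and Bonferroni-adjusted post hoc tests". On reporting, the Statistical analysis section says "The results will be presented as mean differences and 95% confidence intervals (CI"). It does not say whether these intervals are adjusted for multiplicity.

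The Sample size calculation section rests on a single contrast, "a difference between groups in the Victorian Institute of Sport Assessment-Achilles (VISA-A) at 12 weeks of 14 points", with 80% power and 27 evaluable participants per group. On the SD it says only this: "The standard deviation used in the calculations was obtained from a similar clinical trial"; no value is printed.

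**The concern.** The trial asks the same between-arm question at three visits. Single-step Bonferroni holds every contrast to the strictest threshold, 0.05/k for k contrasts. Holm holds only the smallest p-value to that threshold and relaxes it for each later one, at the same overall error rate. Where a difference persists over several visits, the second and third contrasts are therefore tested more strictly than family-wise control requires.

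In a trial of 54 to 60 people that can matter. A sustained difference, present in the short term and at 6 months, is one of the patterns the objectives set out to look for, and it is where the single-step procedure loses most.

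**Working it through.** **Inputs.**
- From the Sample size calculation section: 27 evaluable per group, a difference of 14 points and 80% power. The significance level is taken as two-sided 0.05.
- Assumed: an SD of 18 (back-solved below), a family of three between-arm contrasts (week 6, week 12, 6 months), a correlation between visits of 0.5 to 0.7, and tests that are always carried out.

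**Step 1: the plan's own figure.** The printed total follows from the evaluable number: 54/(1 − 0.10) = 60. The 27 per group cannot be checked independently because the SD is not given, but it can be inverted. With the normal approximation, SD = 14 / [√(2/27) × (1.960 + 0.842)] = 18.4. A t-based calculation gives 18.0, which is used here. With SD 18 the standard error of a contrast is 18 × √(2/27) = 4.90, and the standardised difference is 14/4.90 = 2.86. On 52 degrees of freedom this gives 80% power at two-sided 0.05, as planned.

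**Step 2: Bonferroni with three contrasts.** The threshold is 0.05/3 = 0.0167 for each contrast. The same standardised difference of 2.86 then gives 65% power per visit.

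**Step 3: Holm with three contrasts.** Order the p-values. Compare the smallest with 0.05/3 = 0.0167, the next with 0.05/2 = 0.025 and the largest with 0.05, stopping at the first failure.
- *Error control.* Suppose m of the k hypotheses are true. When a true one is first rejected, at most k − m others have gone before it, so its threshold is at most 0.05/m. Summing over the m true hypotheses gives at most 0.05, whatever the correlation.
- *Dominance.* Any p-value at or below 0.05/k passes every Holm threshold, so whatever Bonferroni rejects, Holm rejects too.
- *First rejection.* Both methods use 0.05/k for the smallest p-value, so the chance of at least one rejection is identical.

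**Step 4: size of the gain.** Simulation of three correlated two-sample t comparisons, at least 60,000 trials per scenario; ranges cover correlations 0.5 to 0.7.

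| True differences (week 6, week 12, 6 months) | Quantity | Bonferroni | Holm |
|---|---|---|---|
| 14, 14, 14 | power per visit | 65% | 72%–73% |
| 14, 14, 14 | power for all three | 40%–46% | 59%–63% |
| 14 at two visits, 0 at the third | power at each of the two | 65% | 68%–69% |
| 7, 14, 10 | week 6 | 16% | 24%–25% |
| 7, 14, 10 | week 12 | 65% | 66%–67% |
| 7, 14, 10 | 6 months | 34% | 40%–41% |
| 7, 14, 10 | power for all three | 10%–12% | 19%–23% |
| 0, 14, 0 | week 12 | 65% | 65% |
| 0, 0, 0 | family-wise error | 3.9%–4.6% | 3.9%–4.6% |

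In no simulated trial did Bonferroni reject a contrast that Holm did not.

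**The case against.** The strongest reply is that nothing here is wrong. Bonferroni controls the family-wise error, no part of the protocol contradicts it, and choosing between two valid procedures is a matter of preference. That stands: the point is an improvement in efficiency and corrects no error.

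A reader might infer that the power is given away for nothing. The documents do not support that. The plan reports mean differences with confidence intervals, and Bonferroni has simple intervals that agree with its tests: for three contrasts, each at 1 − 0.05/3 = 98.3%. Holm has no equally simple counterpart. On the other side, the Statistical analysis section promises only 95% intervals and does not call them simultaneous or adjusted. Ordinary 95% intervals would already not correspond to Bonferroni tests, and in that case Holm gives up nothing the plan offers. The trade-off becomes real only if adjusted intervals are intended.

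A reader might also infer that the procedure alone explains the loss of power, or that Holm would restore the planned 80%. It would not. The fall from 80% to 65% comes from adjusting a sample sized on one unadjusted contrast. Even with the full effect at all visits, Holm recovers 7 to 8 of those 15 points.

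Finally, the all-visits scenario is the favourable one. The sample size assumes 14 points at 12 weeks only. Table 1 has both groups at 55% 1RM in weeks 1–2, with the loads separating from week 3, so a full difference by week 6 is a strong assumption. If week 12 is tested as a single primary contrast, the family has size one and the two methods coincide. These limits hold, and they determine how much weight the point can bear.

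**Conclusion.** The point holds as a cheap improvement. For any family of two or more post hoc contrasts, Holm gives the same guarantee as the planned method and never rejects less. Under the stated assumptions the gain is largest for a sustained difference: about 7 to 8 points of power per visit and 17 to 19 points for showing all three. With uneven differences of 7, 14 and 10 points it is 8 to 9 points at week 6, 1 to 2 at week 12 and 6 to 7 at 6 months. It is nil or immaterial when only one visit differs, and exactly nil for finding at least one difference.

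The dominance result needs no assumptions. The sizes do: the SD, the correlation and the three-contrast family are not given in the protocol article, and the figures would change with them. Which contrasts form the family, and the sizing on one contrast, are separate matters that Holm would not settle.

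**What to change.** In the Abstract (Methods) and in the Statistical analysis section, replace the Bonferroni adjustment with Holm (sequential Bonferroni) adjustment for the post hoc tests within each outcome. Keep the planned mean differences and 95% confidence intervals, and state whether those intervals are unadjusted.

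The cost is a change of wording in two places. No extra participants, visits or data are needed, and the change can be recorded before the final data collection planned for July 2026. The one real downside concerns intervals: Holm-adjusted p-values have no simple matching simultaneous intervals. If the sponsor intends Bonferroni-adjusted intervals, some may not agree with the Holm tests, and the sponsor should weigh that agreement against the gain in power before changing.

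### The missing-data sentence, on its plain reading, is a single regression fill analysed as observed data, which would make intervals too narrow or shrink the treatment effect

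*Protocol article*

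**What the plan says.** Everything on missing data is in the Statistical analysis section of the Protocol article. The principle is stated as "All data will be analyzed using the intention-to-treat principle", and the same sentence continues that "in the event of missing data, a regression-based imputation technique will be used", with one literature reference. The model is described thus: "Outcome measures will be analyzed using generalized estimating equations (GEE) to identify main effects of group and time, and group-by-time interactions". Results are to be given as mean differences with 95% intervals, with Bonferroni post hoc tests where appropriate.

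The Sample size calculation section gives the only loss figure: "Considering a loss of 10%, we reached a total number of 60 individuals, with 30 in each group". That calculation is said to be for linear mixed models and targets "a difference between groups in the Victorian Institute of Sport Assessment-Achilles (VISA-A) at 12 weeks of 14 points". On the SD it says only: "The standard deviation used in the calculations was obtained from a similar clinical trial that used this same variable as the primary outcome". No value is given for it, nor for the correlation between visits.

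The Outcomes section schedules VISA-A at baseline, week 6, week 12 and 6 months after the interventions end.

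**The concern.** The article names a method for missing outcomes and then describes one ordinary analysis. Nothing mentions several completed datasets, a random error added to predictions, or pooling of variances. A reader following the text would fill each gap once from a regression and run the GEE on 60 apparently complete participants.

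That can go wrong in two ways:

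- **Group in the imputation model.** The filled values add no information, but the analysis counts them as if they did. The standard error is too small and the interval too narrow.
- **Group left out.** Filled values in both arms come from one common regression, so the arms are pulled together and the difference shrinks.

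Both affect the primary outcome. The trial is sized on a 14-point difference, and the Outcomes section uses 14 points as its threshold for meaningful VISA-A improvement, so shrinkage can matter to the conclusion. The 6-month assessment belongs to the primary objectives, yet loss at that visit has no planning figure of its own.

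**Working it through.** **Inputs from the article.** 30 per group randomised (27 before loss), 10% loss, difference 14 points, power 80%, alpha 0.05 (two-sided assumed).

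**Inputs assumed.** SD, correlation between visits, and the missingness mechanism.

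**Step 1: the plan's own figures.** 54 / 0.90 = 60, as stated. The 54 cannot be checked independently without the SD. Solving backwards with a simple two-group comparison:

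SD = 14 / [(1.960 + 0.842) × √(2/27)] = 14 / 0.7625 ≈ 18.4; with the t distribution it is 18.0.

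An SD of about 18 is therefore consistent with the stated size.

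**Step 2: why the standard error is too small with group in the model.** Consider one visit analysed by ANCOVA (3 parameters) as a simplified stand-in for the GEE. A deterministic fill from the same model leaves the estimate and residual sum of squares unchanged, but raises the residual degrees of freedom and the count per arm. The reported SE is then approximately the available-data SE times

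√[(df observed / df filled) × (n observed / n filled)].

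At 10% loss: √[(51/57) × (27/30)] = √0.805 = 0.897. The available-data SE is 4.33, and 4.33 × 0.897 = 3.88, which is the simulated value. At 20% loss: √[(45/57) × (24/30)] = 0.795, and 4.60 × 0.795 = 3.66 (simulated 3.65).

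**Step 3: why the effect shrinks without group.** If baseline is the only predictor, a filled value carries no treatment contrast, so the difference is roughly 14 × (1 − fraction missing): 12.6 at 10% and 11.2 at 20%. If week 6 is also a predictor, it carries part of the contrast and the shrinkage is milder.

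**Step 4: simulation, set-up A.** ANCOVA at one visit, SD 18.3, correlation 0.5, missing completely at random and equally by arm, 4,000 trials per scenario. Estimate, SE and coverage are under a true difference of 14; null rejection is under a true difference of 0.

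| Loss | Method | Mean estimate | Mean reported SE / empirical SE | Coverage | Null rejection |
|---|---|---|---|---|---|
| 10% | Available data, no imputation | 14.07 | 4.33 / 4.40 | 95.1% | 4.6% |
| 10% | Single fill, with group | 14.07 | 3.88 / 4.40 | 91.7% | 7.1% |
| 10% | Single fill plus random error, with group | 14.03 | 4.09 / 4.61 | 91.7% | 7.1% |
| 10% | Single fill, without group | 12.63 | 3.93 / 3.96 | 93.6% | 4.8% |
| 10% | Multiple imputation (20), Rubin's rules | 14.07 | 4.36 / 4.41 | 95.3% | 4.5% |
| 20% | Single fill, with group | 14.04 | 3.65 / 4.70 | 87.7% | 11.9% |
| 20% | Single fill, without group | 11.18 | 3.73 / 3.75 | 87.6% | 5.0% |
| 20% | Multiple imputation (20), Rubin's rules | 14.04 | 4.66 / 4.73 | 95.2% | 4.6% |

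At 10% loss with group, 3.88 / 4.40 = 0.88, so the SE is about 12% too small.

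**Step 5: simulation, set-up B.** Repeated measures, SD 18, exchangeable correlation 0.3 and 0.5, dropout at random after week 6, and week 12 regressed on baseline and week 6 (6,000-10,000 runs).

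- With group, 10% loss: SE ratio 0.887 and 0.923, coverage 91.7-93.0%, null rejection 7.9-8.5%, against about 6% without the imputation.
- With group, 20% loss: SE ratio 0.826 and 0.853, coverage 89-91%, null rejection 11-12%.
- Without group: 12.82-12.86 at 10% loss and 11.71-11.81 at 20%.

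A further run with a GEE-type robust SE gave null rejection of about 8.5% at 10% loss with group, against about 6% with no missing data, and an estimate of about 12.9 without group. The excess of 6% over 5% is small-sample GEE error, not an imputation effect.

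**The case against.** The strongest reply is that the article never says the imputation is single. The cited reference and the ethics-approved full protocol are not available here. Regression-based multiple imputation fits the same words, and in set-up A it kept coverage at 95.2-95.7% and null rejection at 4.3-4.6% across 10-30% loss. The number of imputations, the variables in the model and the pooling rule are also details that a journal article commonly leaves to an analysis plan.

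Most of this stands. A reader might infer that the planned intention-to-treat intervals are wrong, or that group is omitted from the imputation model. The document supports neither: it does not say that predictions are inserted without error, that the filled data are analysed as complete, or which predictors are used. Nor does it project 20% loss; the figures at that level show sensitivity only. At the planned 10%, the harm is modest: about 1.4 to 3.3 points of coverage in set-up A, and without group there is attenuation but no excess of false positives.

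What does not stand is that this is mere silence. The article states a method and the analysis that follows it, and carrying these out on their plain reading gives an invalid result. Adding a random error to a single fill does not repair it, as the table shows.

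**Conclusion.** The point holds conditionally, with moderate confidence. The sentence permits, and most plainly describes, a procedure that understates uncertainty if group is in the imputation model and attenuates the effect if it is not. The planned 10% loss is enough to produce either fault, and both grow with the missing fraction, so the 6-month comparison is the more exposed if loss there exceeds 10%.

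The sizes rest on an SD of about 18 (back-solved, not stated), correlations of 0.3-0.5, and loss that is completely at random or at random. Set-up A also uses a single-visit ANCOVA in place of the GEE. If the cited technique is multiple imputation with a suitable model and pooling, the defect disappears and only the wording needs attention.

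**What to change.** Replace the imputation clause with one of the following, before the final data are analysed.

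- **(a)** A likelihood-based linear mixed model on all observed data from all randomised participants, without outcome imputation. It is valid under missing at random and matches the stated basis of the sample size.
- **(b)** Keep the GEE and use multiple imputation, with group, baseline and all visit scores in the imputation model and estimates pooled by Rubin's rules.

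Dropping the imputation while keeping an unweighted GEE is not a full substitute, because that analysis generally needs data missing completely at random. A delta-adjusted sensitivity analysis for dropouts is optional.

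The cost is a changed sentence, a little more analyst time and slightly wider intervals. In set-up A at 10% loss, the mean SE is 4.36 with multiple imputation against 3.88 with the single fill, and the empirical SE is about 4.4. If the intended technique is already multiple imputation, saying so in the terms of (b) is enough.
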